## Data quality and control

To enable simple and accurate data entry and processing, hard copy of the CRFs will feature numbered and coded items. The principal investigators will review versions of the forms before they are finalized. To guarantee thorough data collection, standard operating procedures along with the templates will be created, and the research scientists working as field personnel will receive the necessary training. This will involve assessing their own performance through quality control, which involves looking for any missing information or improbable answers. Additionally, after data collection, principal investigators will do additional quality control checks to ensure that the collected data are complete, consistent and comprehensive. Before the CRFs are used for data documentation necessary corrections/modifications will be made.

### Standardization of the quality of laboratory and imaging assessments

Serum AMH levels will be measured through electrochemiluminescence immunoassay (ECLIA) on a cobas® e 602 analyzer (Roche diagnostics, Germany). Using Beckman Coulter AMH Gen II ELISA (unmodified version, without predilution), the assay will be standardized prior to use. To ensure accurate calibration and traceability of results, through the relevant CalSet, the predefined master curve will be adapted. The assay calibration will be performed once per reagent lot (using a fresh reagent each time, preferably not more than 24 h since the analyzer has registered using the cobas e pack). This calibration interval will be dependent on the result verification done on each laboratory and for the renewal, certain conditions will be prespecified and recommended before next use, such as, if using the same reagent lot, the assay will be calibrated after 12 weeks, and if same cobas e pack is used in the analyzer, calibration will be done after 28 days. The QC analysis on each lot will be performed using PreciControl AMH. For this, the controls for each of the standard AMH concentrations will be done once every 24 h or once per cobas e pack, following the calibration protocol mentioned above. The validated measuring ranges for the appropriate clinical use will be set as 0.01–23 ng/mL.

The assessment of antral follicles by will be done by transvaginal ultrasonography using a high-resolution ultrasound machine (LOGIQ P5, GE Healthcare, USA) with a transvaginal probe operating at 6–8 MHz. In order to guarantee the consistency, the same ultrasound equipment will be used throughout the study period. To reduce inter-observer variability, a single operator with over 15 years of pelvic ultrasonography experience will perform all scans. As advised by the manufacturer, the ultrasound equipment will receive routine calibration and preventive maintenance.

## Data security

All participant data will be internally documented using unique identifier codes to maintain confidentiality. Access to these identifiers will be restricted to the core research team, including the Principal Investigator, Co-Investigators, and Project Scientists directly involved in the study. Other than the hardcopy the data will be encrypted on a hard drive with a password. None of the details that reveal the identity of the participant will be stored in the database. All data will be accessed using the anonymous codes that are assigned to each participants who are involved in the clinical trial. Additionally, the follicular fluid samples collected from these individuals will be assigned with the same coding and these will be recorded in a paper and stored in the server with passwords. The data collected after the follicular fluid data analysis will be given utmost security, that none of these would be made available in public domain. If the data generated is used for publication process, the identity of the participant will be kept anonymous and none of the personnel data will be shared. However, few data including the participant’s previous IVF history and demographic information will be used in the publication on a case basis. Nevertheless, all the sensitive information regarding the participant and the samples collected will be secured.

## Data storage

After completing the study, all the files related to the study will be stored in a server and in an encrypted hard drive. The analog CRFs will be kept locked in cupboards for storing it for long term. Both the electronic and hard copy of all the data will be stored for a minimum of 10 years after the study completion and frequent checks will be done to ensure that the data is accessible and available. The multiomics data of the collected samples will be stored in a encrypted storage device. The raw proteomics mass spectrometry data will be submitted to ProteomeXchange consortium (32) via the PRIDE (33) partner repository. After submitting the raw data, a dataset identifier number will be provided, and it will be available with a accession number in the PRIDE repository.

## Statistical methods

The AMH and AFC changes within the 30 participants who underwent Ayurveda treatment will be assessed using paired *t*-tests (if the data is normally distributed) or Wilcoxon signed-rank test (if the data is non-normal), as determined by Shapiro–Wilk test. Statistical significance is considered as *p* < 0.05 for all two-sided tests. Results will be reported as mean ± SD or median (IQR), with effect sizes (Cohen’s d) for pre-post changes. As a sensitivity analysis, ANCOVA will be utilized for adjusting post-treatment data for baseline AMH/AFC and variables such as age, BMI, and ovarian response.

Follicular fluid from 10 control participants and 10 Ayurvedic-treated participants chosen from the 30-participants treatment arm and matched according to age and baseline AMH/AFC will be obtained for the secondary, exploratory multi-omics analysis. All the laboratory experiments will be performed in triplicates (of each biological samples) and statistical analysis will be done using GraphPad Prism software. The statistical analysis of collected proteome data will be performed using Proteome Scaffold software (version 4). Peptide identifications will be accepted if they can be established at greater than 95.0% probability. The Scaffold Local FDR algorithm and peptide prophet algorithm with scaffold delta-mass correction will assign peptide probabilities. Protein identifications will be accepted if they can be established at greater than 99.0% probability and contain at least two peptides representing the protein family. The protein prophet algorithm will assign protein probabilities (34, 35). For metabolomics analysis, after data generation, the heatmaps, principal component analysis, and multivariate statistical analysis will be performed using R (Version 4.5.1) and MetaboAnalyst 6.0. To evaluate the differences between the treatment and control groups in transcriptomics, proteomics, and metabolomics, *t*-tests (for normally distributed data) or Mann–Whitney U tests (for non-normal data) will be used for each gene, protein, or metabolite. To account for multiple comparisons, the Benjamini–Hochberg FDR correction will be used; an FDR of less than 0.05 will be considered significant. As described under each section, specific assays will be used to further validate the most important genes and proteins. No formal sample size calculation was performed for the exploratory multi-omics analysis, as it is hypothesis-generating, and the 10 treatment samples were selected based on matching and feasibility.

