**Materials and methods:**

An open label single arm trial will be conducted to explore the role of an Ayurveda treatment protocol as a prerequisite for IVF in women with DOR. Forty women diagnosed with DOR satisfying eligibility criteria will be recruited to the study. Out of them, thirty participants will be undergoing Ayurveda treatment prior to their next IVF, and ten participants will be assigned to control group for follicular fluid analysis. Within subject change in serum anti-mullerian hormone and antral follicle count will be the primary outcomes evaluated. The multiomics analysis of follicular fluid will be done in 20 participants recruited to the study (treatment group 10 and control group 10).

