## Materials and methods

This is a prospective, exploratory, single-arm, open-label, single-centred study, coordinated by Amrita Fertility Centre, Amrita School of Ayurveda, and Amrita School of Biotechnology, India with two assessment points (baseline and post-intervention). Participants are women diagnosed with DOR undergoing fertility treatments. Women under the age of 40 satisfying all the eligibility criteria and willing to provide informed consent will be recruited from Amrita Fertility Centre, Kochi. Recruited participants will be admitted at Amrita School of Ayurveda, Kollam to undergo a standardized Ayurvedic treatment protocol for a maximum period of 21 days. Following the inpatient treatment, participants will be advised to continue prescribed internal medications for an additional 1 month. After undergoing Ayurveda treatment, participants will be sent back to Amrita Fertility Centre for post-assessment and further fertility treatments, during which follicular fluid will be collected for multi-omics analysis. Figure 1 depicts the trial’s participant flow. The Standard Protocol Items: Recommendations for Intervention Trials (SPIRIT) declaration is followed while reporting the protocol (22). The institutional ethical committee approved the study and is prospectively registered under ctri.nic.in with the number CTRI/2023/11/059872 on November 15, 2023.

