### Sample size

The sample size calculation was done using G*Power (version 3.1.9.7) (23) based on a previous study data. The initial sample size calculated to detect an effect size of 0.58 for a two-sided significance level of 0.05 and 80% power was 26. To account for feasibility considerations and an anticipated 20% dropout, the final sample size was set at 30 participants. Since the present study is planned as an exploratory study, this sample size is not meant to give confirmatory inference, rather this study is planned to provide preliminary data regarding the role of an Ayurvedic treatment protocol in women with reduced ovarian reserve.

Follicular fluid will be collected from 10 participants who undergo Ayurveda treatment and 10 control participants who is receiving a contemporaneous IVF stimulation protocol for performing multi-omics analysis (matched by age and baseline AMH/AFC). No formal sample size calculation was performed for the multi-omics analysis, as it is hypothesis-generating and intended for exploratory purposes. Because the 10 controls included are for exploratory multi-omics analysis only, no clinical inference will be drawn between treatment and control groups.

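### The ANCOVA sensitivity analysis has no group contrast in this single-arm design, so it cannot give an adjusted treatment effect or show that the mean change is robust to baseline, age or BMI

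*Protocol article*

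**What the plan says.** The Materials and methods section describes a "prospective, exploratory, single-arm, open-label, single-centred study" with two assessment points. The Statistical methods section gives the main analysis: "The AMH and AFC changes within the 30 participants who underwent Ayurveda treatment will be assessed using paired" t-tests, or the Wilcoxon signed-rank test if the Shapiro–Wilk test indicates non-normality. It then adds: "As a sensitivity analysis, ANCOVA will be utilized for adjusting post-treatment data for baseline AMH/AFC and variables such as age, BMI, and ovarian response". It names no group factor, no contrast and no covariate value at which the adjusted figure is to be read.

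The only other women in the study are the controls. The abstract says that "ten participants will be assigned to control group for follicular fluid analysis", and the Sample size section says that "no clinical inference will be drawn between treatment and control groups".

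**The concern.** ANCOVA normally estimates a difference between groups with covariates held equal. Here there is one group and the question is whether its mean moved. Covariates recorded once per woman cannot shift that mean when it is read at their own averages.

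A sensitivity analysis should be able to give a different answer when an assumption changes. This one cannot give a different estimate, yet its p-value can be smaller than that of the paired test. A reader who sees the two agree may think that the change has survived adjustment for baseline, age and BMI.

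A real threat is left untouched. The Inclusion criteria select women on low AMH and/or low AFC, and Trial settings describes recruitment of eligible women after the baseline assessment, so the qualifying value may itself be the baseline. Some rise is then expected without any treatment effect.

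**Working it through.** **1. The plan's own figure.** Inputs from the Sample size section: "The initial sample size calculated to detect an effect size of 0.58" with a "two-sided significance level of 0.05 and 80% power was 26". Taking 0.58 as mean change divided by the SD of change, the noncentrality at n = 26 is 0.58 × √26 = 2.96. The exact two-sided paired t-test then has power 81.1%; n = 25 gives 79.5%. So 26 reproduces, and the planned effect is a within-woman change.

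**2. Is a group effect available?** The 30 treated women are all in one arm. The ten controls are reserved for follicular fluid analysis, and clinical inference against them is excluded. There is none.

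**3. What the model estimates.** In least squares with an intercept, residuals sum to zero, so intercept = mean(outcome) − Σ slope × mean(covariate).
- Post value on mean-centred covariates: the sum is zero and the intercept is the post mean.
- Change on mean-centred covariates: the intercept is mean(post − baseline), the paired mean change.
- Post value on uncentred covariates: the intercept is the prediction at AMH 0, age 0 and BMI 0.

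The two centred models are the same fit: residuals agree, the baseline slope differs by exactly 1, and the intercepts differ by the baseline mean.

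**4. Numerical illustration.** The documents give no SDs, so these inputs are assumed: n = 30; true AMH mean 0.7, SD 0.25; measurement SD 0.15 at baseline and 0.20 after treatment; age 34 (SD 4), with 0.01 lower post AMH per year; BMI 25 (SD 4); 0–3 oocytes. One data set with true change 0.15, then 4,000 runs per scenario:

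| Analysis | Estimate (SE), p, one data set | Rejects, no change | Rejects, change 0.15 |
|---|---|---|---|
| Paired t-test | 0.127 (0.038), 0.0024 | 4.8% | 88.3% |
| Change, centred | 0.127 (0.030), 0.0003 | 6.4% | 90.0% |
| Post, centred | 0.802 (0.030), <0.0001 | 100% | 100% |
| Post, uncentred | 1.65 (0.41), 0.0005 | 17% | 25% |

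In every run the centred change intercept equalled the paired mean change (largest difference below 1e-15). Its standard error was about 6% smaller on average, because the model treats the covariate means as fixed. The centred post model tests whether mean AMH is zero, which is not a question of this trial.

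**5. Regression to the mean.** Let ρ be the test–retest correlation and μ the mean of the unselected reference population. With no treatment effect, expected change = (1 − ρ)(μ − baseline mean). Neither ρ nor μ is in the documents. Suppose women are selected for a baseline more than 0.5 SD below μ. Their baseline mean is then φ(0.5)/Φ(−0.5) = 0.352/0.309 = 1.141 SD below μ, with variance 1 + 0.5 × 1.141 − 1.141² = 0.268. The SD of change is √[(1 − ρ)² × 0.268 + 1 − ρ²].

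| ρ | Expected change (baseline SD) | SD of change | Ratio |
|---|---|---|---|
| 0.6 | 0.4 × 1.141 = 0.456 | 0.826 | 0.55 |
| 0.8 | 0.2 × 1.141 = 0.228 | 0.609 | 0.37 |
| 0.9 | 0.1 × 1.141 = 0.114 | 0.439 | 0.26 |

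The last column is on the same scale as the planned 0.58. By step 3, the ANCOVA read at the sample means carries the same shift as the paired change.

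**6. Ovarian response.** The Inclusion criteria confine the qualifying previous cycle to at most three oocytes. In Table 1, oocyte pick-up in the next cycle is Visit 4, after the Visit 3 outcome. The Statistical methods section does not say which response is meant.

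**The case against.** The best defence has four parts.

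*The model is not empty.* A reader might infer that it tests nothing. That is too strong. The centred change model tests whether mean change is zero, with its own standard error, and the slopes test whether change depends on baseline, age or BMI (in the example, p = 0.02 for baseline and 0.01 for age). This stands, but the article offers the model as a sensitivity analysis, not as a search for predictors.

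*It could handle regression to the mean.* A reader might infer that regressing post on baseline can never do so. It can, if baseline is centred at the reference mean μ. Under the selection in step 5 with no treatment effect, that intercept is zero on average. The price is precision: at ρ = 0.8 its standard error is √[0.36 × (1/30 + 1.141²/(30 × 0.268))] = 0.26 SD, against √(0.36/30) = 0.11 at the sample mean. The article gives no reference mean, so as written this correction is not made.

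*Ovarian response may be usable.* Counts from 0 to 3 still vary, and the post-treatment reading is only one possibility. The documents support calling the covariate undefined and range-restricted, not unusable.

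*It is one sentence in a condensed article on an exploratory study.* Centring and model form are commonly left to an analysis plan, and the Limitations section calls the findings preliminary. Nothing says that the ANCOVA will be reported as proof of robustness; that harm is a risk, not a stated intention. But further detail elsewhere cannot supply a comparison group, and relabelling is needed even though the relabelled model is algebraically the same fit.

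**Conclusion.** The point holds in this form: the named ANCOVA has no group contrast, cannot yield an adjusted treatment effect, and cannot serve as a check on the mean change. At the sample means, its estimate is the post mean or the paired mean change. That is an identity and rests on no assumed value. The 6% smaller standard error and the 6.4% against 4.8% type I error do rest on assumed data and show direction only.

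The regression-to-the-mean range of 0.26 to 0.55 SD of change rests on an assumed cut-off and correlations, and on the qualifying value being the baseline. It shows that the shift could be a material part of the planned 0.58, not that it will be.

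The paired main analysis and the stated 26 are unaffected. The change is worth making but modest, in proportion to an exploratory trial.

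**What to change.** 1. Describe the model as a regression of change on mean-centred baseline, age and BMI that explores who changes. State that its intercept is the mean change, and do not cite it as a robustness check.
2. Define ovarian response as the pre-treatment response in the previous cycle, or drop it. Do not use the Visit 4 response.
3. As the sensitivity analysis, report the mean change with its 95% CI after subtracting (1 − ρ)(μ − baseline). For fixed ρ and μ this can be computed per woman and averaged. Show it over a stated range of ρ and μ, including ρ = 1 (no shift). Declare both as assumptions: the documents give neither, and Table 1 shows only eligibility screening at Visit 0, with no separate AMH or AFC value from which to estimate ρ.

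This changes analysis wording and adds a small table; it needs no new visits or data. The downside is that the corrected change may be smaller than the paired one.

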### Multiomics analysis methodology

#### Transcriptomics of granulosa cells

Follicular fluid collected will be aspirated and pooled during the retrieval of oocytes. Granulosa cells will be isolated from the follicular fluid by centrifugation at 700 g for 10 min using percoll-mediated density gradient centrifugation. The layer with the cells will be carefully removed using a pipette and transferred to a fresh tube with the cell storage medium (10% FBS with DMSO). Total RNA will be extracted from the cells using TRIzol reagent. RNA purity and concentration will be assessed using Nanodrop2000 spectrophotometer (Thermo Fischer Scientific) with samples showing A260/280 between 2.0 to 1.8 considered acceptable and outsourced to MedGenome, Bangalore, India for library preparation and RNA sequencing. The quality of the raw reads will be checked using FastQC and MultiQC. Adapter trimming and low quality read removal will be performed using Trimmomatic v0.39 and the resulting clean reads will be aligned to the human reference genome with STAR (v2.7.10a). Gene counts will be obtained with feature Counts (v2.0.3) and analysed using DESeq21.34.0 in R software. Differential gene expression profiles will be analyzed comparing the control and treatment samples. False positives will be analyzed through Benjamini–Hochberg correction method. The adjusted *p*-value (FDR) less than 0.05 will be considered statistically significant. Following normalization, the gene enrichment analysis will be performed. The top upregulated and downregulated genes (≥1.5-fold) will be further validated using qRT-PCR using specific primers for the selected genes. The relative quantification of genes will be performed through comparative CT analysis.

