100 μg of protein samples will be used for in-solution protein digestion. To achieve this, reduction will be performed using dithiothreitol (100 mM, incubated at 56 °C for 45 min) and alkylation using iodoacetamide (250 mM, incubate for 30 min at RT in the dark). The resulting solutions will be digested using trypsin (1:20 ratio), followed by incubation at 37 °C overnight. The digestion process will be terminated after 16 h by adding 0.1% FA. The solution containing the digested peptides will be subjected to TMT labelling (10 plex) for protein quantification (31). The TMT labelled peptide samples will be desalted and subjected to mass spectrometry analysis. The peptides will be resolved through a C-18 reversed phase column (Agilent ZORBAX SB-C18, 75 μm × 150 mm, 5 μm) having a 40 nL enrichment column also. The samples will be infused to the mass spectrometer through a capillary/nano HPLC equipped with a chip cube source. The mass spectrometric data will be collected in positive ionization mode. The mobile phase solvents will be; A-water+ 0.1% formic acid; B-acetonitrile: water in 90:10 ratio. The enzymatic digests will be resolved across the column using a linear gradient of 5–45 %B in 30 min; 45–90 %B in 20 min. The other parameters that will be used for the data acquisition are: MS; 250–3,000 m/z, MS/MS; 50–3,000, collision gas-nitrogen, capillary voltage; 2000 V, dry gas; 5 L/min, fragmentor voltage; 150 V, source temp; 350 °C, MS and MS/MS scan speed; 4 & 3 spectra/s, respectively. Number of precursors; 5, preferred charge states; trypsin (2, 3, >3). The data will be acquired using MassHunter (Version 6.0) software from Agilent Technologies. The raw data obtained after MS analysis will be analysed using MassHunter, Mascot and Proteome Scaffold using the Swissprot database. The following parameters will be set during data analysis: MS tolerance; 10 ppm, MS/MS tolerance; 20 ppm, cysteine (carbamidomethylation; fixed modification), TMT labelling will be also selected as fixed modification. Deamidation of asparagine and glutamine will be used as variable modifications, number of missed cleavages; 2, charge states (2^+^, 3^+^, 4^+^) for trypsin, decoy option will be enabled during the analysis. Proteome Scaffold will be used to statistically validate the proteins and peptides identified through Mascot searches as described under the statistical methods section. Protein data will be filtered at 5% FDR and normalized for downstream quantitative analysis. The differentially expressed proteins will be selected after the quantification and selected top proteins (≥1.5-fold) will be further validated through ELISA and Western blotting using the specific primary antibodies using the same follicular fluid samples.

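### Genes are given two different between-group tests at the same FDR with no hierarchy, and no stated between-group test uses the factors on which the groups are matched

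*Protocol article*

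**What the plan says.** All references are to the protocol article.

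- **Transcriptomics of granulosa cells.** "Gene counts will be obtained with feature Counts (v2.0.3) and analysed using DESeq21.34.0 in R software". The contrast is stated next: "Differential gene expression profiles will be analyzed comparing the control and treatment samples". Benjamini-Hochberg correction follows, with adjusted p below 0.05 as the criterion. The top genes with at least 1.5-fold change go to qRT-PCR.
- **Statistical methods.** The scope sentence opens "To evaluate the differences between the treatment and control groups in transcriptomics, proteomics, and metabolomics", so it covers transcriptomics. The t-test applies to normally distributed data; otherwise Mann-Whitney U "tests (for non-normal data) will be used for each gene, protein, or metabolite". Benjamini-Hochberg is applied with FDR below 0.05.
- **Groups.** Ten treated and ten control women, the treated women being "chosen from the 30-participants treatment arm and matched according to age and baseline AMH/AFC". Sample size names the same matching factors. Neither section says whether matching is in pairs or by group.
- **Proteomics of follicular fluid.** "The solution containing the digested peptides will be subjected to TMT labelling (10 plex) for protein quantification".
- **Status.** Sample size and Statistical methods call the omics work hypothesis-generating, with no formal sample-size calculation. Sample size adds that no clinical inference will be drawn between the groups.

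**The concern.** The same genes, contrast and FDR threshold are governed by two rules. DESeq2 is a negative-binomial count model that shares dispersion information across genes. The other rule is an unmoderated two-sample test whose form depends on each gene's apparent normality. With ten women per group the two will generally select different genes. Nothing says which list is reported or that one is a sensitivity analysis, so the choice could be made after both are seen. The chosen list goes on to qRT-PCR and to the pathway analysis described under Integration of multiomics data.

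The second issue is the matching. The design controls for age and baseline AMH/AFC when women are selected, but no stated between-group analysis uses that information. At 10 v 10, variance that could be removed is worth removing.

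**Working it through.** **1. Two rules for genes.** The article gives no sample size, power or detectable effect for the omics comparison, so there is no figure to reproduce. The check is a comparison of text:

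| | Transcriptomics section | Statistical methods |
|---|---|---|
| Unit | gene counts | each gene (also protein, metabolite) |
| Contrast | control v treatment | treatment v control |
| Test | DESeq2 | t-test or Mann-Whitney U, by normality |
| Threshold | BH-adjusted p < 0.05 | BH FDR < 0.05 |
| Hierarchy | none stated | none stated |
| Matching term | none stated | none (independent-sample tests) |

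**2. Effect of leaving out the matching.** Suppose pairs with within-pair correlation ρ and n = 10 per group. The true variance of the mean difference is 2σ²(1 − ρ)/n, whereas the unpaired test assumes 2σ²/n. The true standard error is therefore √(1 − ρ) times the assumed one: √0.7 = 0.84 at ρ = 0.3 and √0.5 = 0.71 at ρ = 0.5. Simulated type I error at nominal 5% (100,000 normal data sets per row; ρ values are assumptions):

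| ρ | unpaired t | Mann-Whitney |
|---|---|---|
| 0 | 5.0% | 4.4% |
| 0.3 | 2.2% | 2.0% |
| 0.5 | 0.9% | 0.8% |

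The error is in the conservative direction and costs precision.

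**3. Mann-Whitney floor.** The smallest exact two-sided p at 10 v 10 occurs at complete separation: 2/C(20,10) = 2/184,756 = 1.08e-5. Benjamini-Hochberg accepts k features at p if p ≤ k × 0.05/m, so k = ceiling(p × m/0.05). The article gives no feature count, so m is assumed.

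| m | 0.05/m | p × m/0.05 at the floor | k |
|---|---|---|---|
| 10,000 | 5.0e-6 | 2.17 | 3 |
| 20,000 | 2.5e-6 | 4.33 | 5 |
| 25,000 | 2.0e-6 | 5.41 | 6 |

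A single feature passes alone up to m = 0.05/1.08e-5 ≈ 4,618. The k values suppose that every gene is tested by Mann-Whitney; a t-tested gene with an equal or smaller p also counts towards k. Genes just short of full separation have p = 2.17e-5, and at m = 20,000 they need 2.17e-5 × 20,000/0.05 = 8.7, so 9 genes.

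**4. What the floor costs.** Average power was simulated with independent normal features, m = 20,000, BH 5%, and 10 runs per setting, so the figures are approximate:

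| Genes shifted | Shift | t-test | Mann-Whitney |
|---|---|---|---|
| 5% | 2 SD | 79% | 71% |
| 5% | 1.5 SD | 30% | 22% |
| 5% | 1 SD | 0.5% | 0.2% |
| 1% | 2 SD | 50% | 39% |
| 1% | 1.5 SD | 5.5% | 1.0% |

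**5. TMT plexes.** 20 women/10 channels = 2 runs at least. That leaves no spare channel for a reference sample.

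**The case against.** The transcriptomics section could be read as the specific rule and Statistical methods as a loose summary. That is plausible, but the latter names transcriptomics and each gene explicitly, so the text does not settle it. The exploratory label is also fair and limits the stakes. It does not remove the conflict, because both rules declare significance.

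Several stronger readings are tempting, and the documents do not support them:

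- *Mann-Whitney can barely reach FDR 0.05 at 10 v 10.* Benjamini-Hochberg is a step-up procedure, so 0.05/m is the bar only for a lone discovery. The floor does not bind at plausible protein or metabolite counts. Five fully separated genes suffice at 20,000. At a 1 SD shift the t-test is nearly as weak, so the sample size is the main limit.
- *Mixing discrete and continuous p-values invalidates the FDR.* Discrete p-values are conservative under the null. The cost is power.
- *Only the t/Mann-Whitney tests ignore the matching, and this inflates false positives.* DESeq2 as described has no matching term either, and the distortion runs the other way. With group matching, unpaired tests are acceptable and adjustment is a gain in precision.
- *The differential list drives the MOFA step.* The integration section trains MOFA on the omics data. The differential lists go to pathway analysis and mapping.
- *The missing plex term is an error.* Run layout is detail that an article may leave to the full protocol. What follows from the text is only that 20 samples need more than one 10-plex run.

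**Conclusion.** The point holds in two parts. First, the article fixes two incompatible gene analyses at the same FDR without a hierarchy. This rests on the text alone and needs no assumption. Second, no stated between-group test uses the matching factors. Its size depends on how strongly the matching induces correlation, which the article does not allow one to judge. At assumed within-pair correlations of 0.3 to 0.5, the unpaired t-test runs at 2.2% to 0.9% in place of 5%.

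The Mann-Whitney floor is secondary. It matters for gene-scale testing when true signals are few or modest, under assumed counts of 10,000 to 25,000 genes. The whole point concerns a secondary, hypothesis-generating analysis and leaves the AMH and AFC outcomes untouched. It is worth correcting because the correction is nearly free.

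**What to change.** 1. In Statistical methods, remove genes and transcriptomics from the t-test/Mann-Whitney sentence, and name DESeq2 as the only gene analysis.
2. State whether matching is in pairs or by group. Include pair ID if in pairs, otherwise age and baseline AMH/AFC, in the DESeq2 design.
3. For proteins and metabolites, use linear models on log2 intensities, preferably moderated, with the same matching terms and one averaged value per woman across the triplicates. A signed-rank test is a poor way to honour pairing here: its floor with 10 pairs is 2/2^10 = 0.00195.
4. Before labelling, balance treated and control women across the TMT plexes, and include plex as a block in the protein model. An imbalance cannot be fully repaired afterwards.
5. Keep Benjamini-Hochberg at 5%, and settle all this before the omics data are compared by group.

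**Cost:** wording, free software and no new samples. In a linear model, residual degrees of freedom fall from 18 (20 − 2) to 15 with three covariates, or 14 with a two-plex block added. With pair ID they fall to 9 (20 − 11), provided that each pair stays in one plex. Pairing therefore pays only if the within-pair correlation is real.
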